## 3.5. Participant timeline

Shedule of enrolment, interventions and assessments

| **TIMEPOINT (state unit)** |  |  |  |  |  |
| --- | --- | --- | --- | --- | --- |
| **VISIT NUMBER:** |  |  |  |  |  |
| **ENROLLMENT:** |  |  |  |  |  |
| Eligibility screen | X |  |  |  |  |
| Informed consent | X |  |  |  |  |
| Allocation | N/A |  |  |  |  |
| **INTERVENTIONS:** |  |  |  |  |  |
|  | N/A |  |  |  |  |
| **ASSESSMENTS:** |  |  |  |  |  |
| List basaline variables | X |  |  |  |  |
| List outcomes variables | X |  |  |  |  |
| List other data variables | X |  |  |  |  |

## 3.6. Sample size

## 3.7. Recruitment

In 2023, around 325 heart transplants (HT) were performed in Spain Given a median of 10-15 HT per center and considering that eight centers that routinely perform invasive coronary physiology are participating, data will be analyzed when 100 patients have completed first year follow-up.

## 3.8. Allocation

N/A

## 3.9. Blinding (masking)

### 3.9.1. Blinding mechanism

### 3.9.2. Emergency unblinding

N/A

## 3.10. Data collection

### 3.10.1. Trial procedures and evaluations

Data will be included in an online database specifically designed for the study on platform REDCap (Research Electronic Data Capture).

### 3.10.2. Retention

Clinical conditions, laboratory findings and clinical events will be assessed at one month and one year. A number will be assigned to each patient; their identity will not be disclosed in any case. All shared information will be anonymized. The principal investigator at each center will be responsible for keeping the data anonymized.

## 3.11. Data management

A number will be assigned to each patient; their identity will not be disclosed in any case. All shared information will be anonymized. The principal investigator at each center will be responsible for keeping the data anonymized.

Data will be processed in accordance with the protection legislation in force (Spanish Personal Data Protection and Guarantee of Digital Rights Act 3/2018, and Regulation (EU) 2016/679).

## 3.12. Statistical methods

### 3.12.1. Outcomes

The characteristics of the study population will be summarized through standard descriptive statistics. Continuous variables will be expressed as mean (± standard deviation) or median [interquartile range (IQR)], as appropriate. Discrete variables will be presented as absolute numbers and percentages. For the comparison of means, the Student's t test for independent measures or the non-parametric Mann-Whitney U test (in the case of dichotomous qualitative variables) and the ANOVA or non-parametric Kruskal test will be used as a hypothesis test. Wallis (in the case of non-dichotomous qualitative variables). For the bivariate analysis of the qualitative variables, the Chi-square test or Fisher's exact test will be used. Events will be compared between groups by using Kaplan-Meier curves. Cox regression analysis will be performed to adjust for confounding factors and to evaluate independent predictors of clinical events. A two-tailed p-value of 0.05 will be considered statistically significant. All statistical analyses will be performed by SPSS software version 20.

In 2023, around 325 heart transplants were performed in Spain (3). Given a median of 10-15 HT per center and considering that eight centers that routinely perform invasive coronary physiology are participating, data will be analyzed when 100 patients have completed first year follow-up.

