# 2. INTRODUCTION

## 2.1. Background and rationale

Acute allograft rejection (AAR) is an important cause of morbi-mortality  after heart transplant (HT), particularly within the first year. Advances in immunosuppression, donor heart evaluation, surgical techniques, and post-transplantation care have led to a gradual reduction in AAR and improved survival after HT over time. Endomyocardial biopsy (EMB) is the gold standard method to guide post-HT treatment, as it represents the best tool to identify rejection in orthotopic HT. However, it is usually repeated up to 5 times during the first year - with some variations depending on each center protocol - and it is potentially associated with serious complications.

Several studies have presented the association between AAR, micro-vasculopathy and cardiac allograft epicardial vasculopathy (CAV).  Index of microcirculatory resistance (IMR) measured early after heart transplantation has been significantly associated with the risk of acute cellular rejection (ACR), and patients with IMR≥15 have higher risk of AAR during 2 years follow-up.

The aim of our study is to evaluate if the use of IMR measured at baseline may be useful in guiding care of patients after HT.

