## 3.4. Outcomes

- The **primary outcome** of the study is to evaluate IMR values and number of EMB performed in the first year after HT: Depending on IMR values obtained in the first three months, clinical status and the other complementary tests the physician will be able to modify the number of biopsies established in each center protocol.If the IMR is less than 15, the number of biopsies could be reduced or kept the same. If the IMR is 15 or greater,number of biopsies would be performed as usual per protocol.

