***Biopsies and immunosuppressive therapy***

Based on IMR results:

- If the IMR is less than 15, the number of biopsies could be reduced or kept the same. No immunosuppressive therapy changes would be made.

- If the IMR is 15 or greater, immunosuppressive therapy could be intensified or maintained the same. Number of biopsies would be performed as usual per protocol.

Given the observational characteristics of the study, decisions regarding clinical patient management will depend on physician discretion considering patient clinical condition and other complementary tests.

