***Changes in EMB protocol based on coronary microvascular resistance***

- Each center will specify the number of annual biopsies performed based on IMR values obtained between the first two months after HT.

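### The tests named for comparing biopsy numbers ignore centre, although the usual number is set by each centre's protocol; the IMR groups should be compared within centre

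*Protocol*

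**What the plan says.** **The biopsy number depends on the centre.** Section 2.1 says of biopsy that "it is usually repeated up to 5 times during the first year - with some variations depending on each center protocol". Section 3.4, on the primary outcome, says that "the physician will be able to modify the number of biopsies established in each center protocol", in the light of IMR, clinical status and other tests.

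**Who decides is described in two ways.** Under the heading on changes in the EMB protocol: "Each center will specify the number of annual biopsies performed based on IMR values obtained between the first two months after HT". Under the heading on biopsies and immunosuppressive therapy: "decisions regarding clinical patient management will depend on physician discretion considering patient clinical condition and other complementary tests". Sections 3.3.1 and 3.4 make a reduction below IMR 15 optional and keep the usual number at 15 or above.

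**Size.** Section 3.12.1 gives the basis for analysing 100 patients: "Given a median of 10-15 HT per center and considering that eight centers that routinely perform invasive coronary physiology are participating".

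**Analysis.** Section 3.12.1, repeated under Statistical analysis in the embedded protocol, lists "t test for independent measures or the non-parametric Mann-Whitney U test" for two groups, ANOVA or Kruskal-Wallis for more, and a two-sided 0.05 threshold. Centre appears in none of these. The only adjusted model is Cox regression, and it is for clinical events. Section 3.12.2 lists no additional analyses.

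**The concern.** The listed tests treat the 100 biopsy counts as independent draws from two IMR groups. By the protocol's own account, patients at one centre share a starting number. That can do two kinds of damage.

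- **Confounding by centre.** If centres with a lighter schedule also have more low-IMR patients, the low-IMR group shows fewer biopsies even when no physician changed anything. The reverse pattern hides a real reduction.
- **Lost precision.** Even with the same IMR mix everywhere, schedule differences between centres go into the error term. A comparison within centre would remove them.

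The study hypothesis is that IMR will reduce the number of biopsies, so this affects the central claim.

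**Working it through.** **1. The plan's own figure.** Eight centres × 10 to 15 transplants = 80 to 120, and 8 × 12.5 = 100. The 100 is reproduced as a volume count. No effect size, standard deviation, power or between-centre variation is stated, so nothing further can be reproduced.

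**2. Inputs.**
- From the protocol: 8 centres, 100 patients (12 or 13 per centre), usual number up to 5 and varying by centre, two-sided 0.05.
- Assumed: usual number 3, 4 or 5 with equal chance per centre; extra biopsies Poisson with mean 0.5; low-IMR share either 50% everywhere or drawn between 25 and 75% per centre.

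**3. How the bias arises (illustration).** Suppose half the centres do 3 biopsies and have 75% low IMR, half do 5 and have 25% low IMR, and nobody cuts anything.
- Low-IMR mean = 0.75 × 3 + 0.25 × 5 = 3.5
- High-IMR mean = 0.25 × 3 + 0.75 × 5 = 4.5

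The pooled comparison shows a saving of 1.0 biopsy that does not exist. Within every centre the difference is 0.

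**4. Type I error, no cut anywhere (5,000 simulated trials per setting).**

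| Low-IMR share by centre | Pooled t test | Linear model with centre as factor |
| --- | --- | --- |
| 50% everywhere | about 5% | about 5% |
| 25 to 75% | about 11 to 12% | about 5% |

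A separate simulation used normally distributed schedules with a between-centre SD of 1 or 2, and a low-IMR share varying with SD 1 on the logit scale. It gave 16% and 23% for the pooled test.

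**5. Precision, balanced mix.**
- The variance of 3, 4 or 5 with equal chance is 2/3. With eight centres the expected between-centre part of the pooled variance is about 2/3 × 7/8 = 0.583. Adding the Poisson part gives 0.583 + 0.5 = 1.083.
- Pooled half-width: 1.984 × √(1.083 × (1/50 + 1/50)) = 1.984 × 0.208 = **0.41** biopsies.
- With a centre factor, the information is about 100 × 0.25 × (1 − 8/100) = 23. Half-width: 1.986 × √(0.5/23) = 1.986 × 0.147 = **0.29** biopsies.

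Simulation gives the same two values.

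**6. If the size of the cut also varies by centre (average cut 1, balanced mix).** Coverage of a nominal 95% interval derived from the pooled t test:

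| Cut pattern | Target: these eight centres | Target: a wider population of centres |
| --- | --- | --- |
| 0, 1 or 2 by centre | about 96% | about 80% |
| 0 or 2 by centre | about 96% | about 74% |
| 0, 1 or 2 by patient | not at issue | about 95% |

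With an unbalanced mix the wider-population figures fall to about 74% and 69%. A centre-level t interval on 7 df covers 94 to 96% for that target. In the 0/1/2 case its half-width is about 0.76, against 0.47 for the pooled interval.

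**The case against.** **The decision may be the physician's.** A reader might infer that the reduction is a centre-level decision, so that the study has eight observations rather than 100. The documents do not support that. Section 3.4 and the paragraph on biopsies and immunosuppressive therapy leave the choice to the physician for each patient, and the sentence about each centre specifying a number may only mean that centres report it. This stands. It does not remove the shared starting schedule, which is enough for the two problems above.

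**No confidence interval is planned.** Correct. What is affected is the p-value, and any interval later derived from the same test. Section 3.12.1 also does not assign a test to the biopsy count; the two-group test by IMR is the natural reading, not an explicit statement.

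**The p-value can be valid.** Also correct. With a similar IMR mix across centres and no cut, type I error is about 5%. Simulations that let cuts vary around an average of zero show 19 to 25%, but they need some centres to biopsy low-IMR patients more often because of IMR. The stated rule provides only for reducing or keeping the number.

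**Poor coverage depends on the target.** The 69 to 80% figures apply only if the eight centres stand for a wider population. They were chosen because they "eight centers that routinely perform invasive coronary physiology are participating" does describe them, that is, for routine use of the technique. Treating them as fixed is defensible, so a 7-df analysis is not required as the primary test.

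**A SAP may deal with centre.** It may. But the protocol positively names tests that ignore a centre dependence it describes itself, and the remedy can sit in the SAP.

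**Conclusion.** The point holds in limited form. The named tests leave out a factor that, on the protocol's own description, determines the starting number of biopsies.

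- If schedule and IMR mix both differ between centres, type I error is about 11 to 12% under the main assumptions, and 16 to 23% with larger assumed variation.
- If only the schedule differs, the test is valid, but a derived interval is about 40% wider than needed (0.41/0.29 = 1.41).
- If the size of the cut varies by centre, a derived interval is too narrow only for conclusions beyond these eight centres.

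It would go too far to say that the p-value fails in every case or that the effective sample size is eight. All sizes rest on assumed schedules and IMR mix, because the protocol gives neither. Separately, the passages on who sets the IMR-based biopsy number must be reconciled.

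**What to change.** 1. **Primary comparison within centre.** Compare the biopsy number between IMR groups with a linear model that has centre as a factor, or with a centre-stratified rank test (van Elteren). A count model with centre also serves if its dispersion is estimated: scheduled counts probably vary less than Poisson (in the assumed setting, within-centre variance 0.5 against a mean of 3.5 to 5.5 at the usual schedule).
2. **Report the difference with an interval**, and show the eight centre differences beside it.
3. **Sensitivity analysis for generalising.** Add a random centre-by-IMR slope with small-sample degrees of freedom, or a t interval on the eight centre differences (7 df). The two weight centres differently, so name one in advance.
4. **Record each centre's usual schedule** before IMR is known, and reconcile the passages on who sets the IMR-based number.

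**Cost.** Protocol or SAP wording and one recorded item per centre. The centre factor uses 7 degrees of freedom (98 to 91). A centre lacking one IMR group contributes nothing to the comparison; this arose in about 5% of simulated trials with an unbalanced mix. The sensitivity interval is wider, about 0.76 against 0.47 in the 0/1/2 case.

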**- Secondary outcomes:**

-IMR variation between first three months after HT and one year: Comparison between the values of index of microvascular resistance (IMR) measured by bolus thermodilution technique between the first and 3rd month after HT and one year in the invasive physiological study. IMR may be expressed as mmHg·s.

-Acute cellular rejection: A ≥2R degree according to the 2010 ISHLT system. Two or more focal infiltration points associated with myocyte injury in EMB. Diffuse infiltration with multi-focal myocyte injury with/without oedema, hemorrhage or vasculitis.Time frame: One year.

-Cardiac allograft vasculopathy: Accelerated fibroproliferative process characterized by diffuse, concentric and longitudinal thickening of the intima of the vascular tree of the graft, affecting everything from the major epicardial arteries to the coronary microvasculature.Time frame: 5 years.

-Cardiovascular mortality:Caused by cardiovascular disease or unknown death. Time frame: 5 years.

-Heart failure: Diastolic or systolic heart failure after heart transplant. Time Frame: Five years.

-Inmunosupressive therapy: Changes in any of the inmunosuppresive agents pre-established in each center heart transplant protocol. Time Frame: Five years

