Various studies have demonstrated the association between ACR, microvascular dysfunction (MVD) and cardiac allograft vasculopathy (CAV) (8). IMR is a quantitative and specific index for coronary microcirculation (9-10).  An increased IMR in the graft has been associated with higher all-cause mortality and adverse cardiac events regardless of epicardial vasculopathy (11). Several IMR cut-off (from 15 to >25) have been associated with ACR within the first year after HT. Patients in whom IMR decreases or does not change one year after HT have a higher event-free rate than those patients in whom the IMR increases (12-13). However, no study has evaluated IMR impact on post-HT management. In presence of a low IMR value, EMB could be performed less frequently; on the contrary, if the IMR value is high, immunosuppression therapy could be modified by an earlier administration of mTor-inhibiting drugs or prescribing calcium antagonists, which are known to improve microvascular function.

Our aim will be to assess if post-HT patient management may be safely modified based on IMR value.

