**STUDY DESIGN**

**ENDPOINTS**

*The main objective* of the study is to evaluate IMR values and number of EMB performed in the first year after HT.

S*econdary endpoints* are:

- Analyze the relationship between ACR and IMR.
- Analyze the relationship between CV mortality and IMR.
- Analyze the relationship between CAV and IMR.
- Analyze the relationship between the variation IMR value in the first two months and one year, and cardiovascular events.
- Analyze the relationship between the combined endpoint of ACR, heart failure, re-transplantation, CV mortality and IMR.
- Assessment of immunosuppressive therapy after IMR results.

All endpoints will be evaluated at 1 year, and annually thereafter for up to 5 years.

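### Kaplan-Meier curves for CAV, heart failure, cardiovascular death and the composite without non-cardiovascular death will overstate absolute five-year risk, because competing deaths (and, for CAV, re-transplantation) are censored

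*Protocol*

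**What the plan says.** Protocol section 3.12.1 gives one curve method for events: "Events will be compared between groups by using Kaplan-Meier curves". The later Statistical analysis section repeats it. Regression is to be by Cox model: "Cox regression analysis will be performed to adjust for confounding factors and to evaluate independent predictors of clinical events". Neither section mentions competing events or cumulative incidence.

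Three single endpoints in section 3.4 run to five years:
- CAV: "affecting everything from the major epicardial arteries to the coronary microvasculature.Time frame: 5 years"
- Cardiovascular mortality: "Caused by cardiovascular disease or unknown death. Time frame: 5 years"
- Heart failure: "Diastolic or systolic heart failure after heart transplant. Time Frame: Five years"

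The ENDPOINTS section adds: "All endpoints will be evaluated at 1 year, and annually thereafter for up to 5 years".

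Because unknown deaths count as cardiovascular, a death of known non-cardiovascular cause is the one kind that falls outside cardiovascular mortality.

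The composite appears in two forms. Section 2.2 includes all-cause mortality. The protocol summary table, the ENDPOINTS section and the Definition of events include only cardiovascular mortality.

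On mortality by IMR, the Introduction and Rationale states: "An increased IMR in the graft has been associated with higher all-cause mortality and adverse cardiac events".

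**The concern.** A patient who dies of infection in year 2 can no longer develop CAV or heart failure, or die of a cardiovascular cause. A patient who is re-transplanted can no longer develop CAV in the original graft. Kaplan-Meier for one of these events must censor such patients. It then treats them as if they carried the same future risk as those still followed. The result estimates risk in a population where the competing event does not occur, and that is higher than the proportion of patients who will have the event.

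The study aims to judge whether management can safely be changed according to IMR. Readers will naturally take five-year risks by IMR group from the plotted curves. If competing mortality differs between the groups, the error in those risks differs too.

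**Working it through.** **Inputs.** The protocol gives no five-year rate for CAV, heart failure, death or re-transplantation, so there is no figure of its own to reproduce. All rates below are assumptions. Hazards are constant: c for the event, d for the competing event, over t years.

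**Formulas.**
- One minus Kaplan-Meier, competing events censored: 1 − exp(−ct)
- True cumulative incidence: c/(c+d) × [1 − exp(−(c+d)t)]

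**Five years, c = 0.07.** Kaplan-Meier: 1 − exp(−0.35) = 29.5%, whatever the value of d.

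| d per year | True incidence | Excess of Kaplan-Meier |
|---|---|---|
| 0.03 | 0.07/0.10 × (1 − exp(−0.50)) = 27.5% | 2.0 points |
| 0.05 | 0.07/0.12 × (1 − exp(−0.60)) = 26.3% | 3.2 points |
| 0.08 | 0.07/0.15 × (1 − exp(−0.75)) = 24.6% | 4.9 points |

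**Wider range.** Take the five-year Kaplan-Meier event risk as 10% to 40% and the five-year competing risk as 2% to 30%, each converted to a hazard by −ln(1 − risk)/5. The excess runs from 0.1 to 5.8 points (about 1% to 19% relative). With a competing risk of 5% it is 0.2 points (event 10%) to 0.9 points (event 40%). A simulation of 200,000 patients per setting agrees: for event 30% and competing 25% it gave 30.1% by Kaplan-Meier and 26.4% true, against 30.0% and 26.3% by formula.

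**One year, c = 0.07.** Kaplan-Meier gives 6.8%. True incidence is 6.6% at d = 0.05 and 6.5% at d = 0.08.

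**Between groups.** The effect on the difference depends on both hazards:
- Event and competing hazards both higher in one group (0.05 and 0.03 against 0.10 and 0.08): Kaplan-Meier 22.1% against 39.3%, gap 17.2 points; true 20.6% against 33.0%, gap 12.4 points. Kaplan-Meier overstates the gap.
- Equal event hazard (0.07), competing 0.03 against 0.08: Kaplan-Meier gap 0; true 27.5% against 24.6%, gap 2.9 points. Kaplan-Meier hides a difference in incidence.
- Five-year event risk 30% with competing 10%, against event 20% with competing 25%: Kaplan-Meier gap 10.0 points; true 28.6% against 17.5%, gap 11.1 points. Kaplan-Meier understates the gap.

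**The case against.** The strongest reply is that absolute risk is not a stated target. The secondary objectives ask about the relationship between IMR and each event, and a Cox model with other deaths censored gives cause-specific hazard ratios that answer this. That stands: the hazard ratios are not at fault, and the problem is confined to the absolute risks shown by the curves. It does not remove the point, because the curves are the stated means of comparing groups and they display absolute risk.

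Second, the size rests wholly on assumed rates. This also stands. A competing hazard of 8% per year means 1 − exp(−0.40) = 33% competing loss over five years, which is high. Sampling error is larger than the bias: if 100 patients split evenly (an assumption), the 95% interval around 30% in a group of 50 is ±1.96 × √(0.3 × 0.7/50) = ±13 points. But bias is not reduced by recruiting more patients, and this one can be avoided.

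Third, the only analysis trigger stated is one year of follow-up in 100 patients. At one year the excess is 0.2 to 0.3 points in the example, so the point has no practical weight for that analysis or for one-year ACR. It concerns the five-year curves.

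Fourth, censoring rules are often left to a statistical analysis plan, which is not at hand. That would answer a complaint about missing detail. Here the protocol names the curve method, and a plan that followed it would carry the bias forward.

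**Conclusion.** The concern holds for absolute five-year risk of CAV, heart failure, cardiovascular death and the composite that omits non-cardiovascular death. Under an assumed event hazard of 7% per year and competing hazards of 3% to 8% per year, the overstatement is about 2 to 5 points. It is under about 1 point if five-year competing mortality is about 5% or less. All-cause mortality and the section 2.2 composite that includes it are not affected.

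Three stronger readings are tempting, and the protocol does not support them:
- A reader might infer that the gap between IMR groups is inflated. The examples show it can be overstated, understated or hidden. The Introduction's statement on all-cause mortality makes differing competing mortality plausible but does not establish it for each endpoint. For cardiovascular death the only competitor is non-cardiovascular death, on which the Introduction says nothing.
- A reader might infer that the excess is always larger in the group with higher mortality. In points it need not be: event 10% with competing 25% gives 1.3 points, while event 40% with competing 10% gives 1.9.
- A reader might treat re-transplantation as a competing event throughout. It competes with CAV of the original graft. Section 3.4 does not tie heart failure to the original graft, and a re-transplanted patient can still die of a cardiovascular cause.

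This is a worthwhile correction to secondary outcomes, best made before five-year data exist.

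**What to change.** In section 3.12.1 and the Statistical analysis section, replace Kaplan-Meier with Aalen-Johansen cumulative incidence curves for these endpoints:
- CAV: competing events are death without CAV, and re-transplantation.
- Heart failure: competing event is death without heart failure.
- Cardiovascular death: competing event is non-cardiovascular death only, with follow-up continuing after re-transplantation.
- Composite that omits non-cardiovascular death: competing event is non-cardiovascular death.

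Report the competing events by IMR group. Keep cause-specific Cox hazard ratios for association. Keep Kaplan-Meier for all-cause mortality and for the composite that includes it.

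The cost is slightly more analysis work and possibly software other than SPSS version 20 for the curves. No new data are needed, since the endpoints already require cause and date of death and of re-transplantation.

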# 1. TRIAL SUMMARY

World Health Organization Registration Data Set

| Title | Index microvascular resistance (IMR)-guided management of heart transplantation |
| --- | --- |
| Primary registry and trial identifying number | ClinicalTrials.gov  NCT 06656065 |
| Secondary identifying numbers |  |
| Sources of monetary or material support | No funding. |
| Primary sponsor | Interventional Cardiology Department Miguel Servet University Hospital. Zaragoza, Spain |
| Secondary sponsors (if any) |  |
| Central contact | [name]  Interventional Cardiology Department Miguel Servet University Hospital. Zaragoza, Spain  [name]  [contact] |
| Study officials/Investigators |  |
| Brief title | IMR-HT study |
| Acronym | IMR-HT study |
| Countries of recruitment | Spain |
| Condition(s) or focus of study |  |
| Interventions |  |
| Key eligibility criteria | Age eligibility: 18 years or older  Sex eligibility: Both  Accepts healthy volunteers: No |
| Study design | Study type: Interventional trial  Allocation: Non-randomized  Intervention model: Single group  Primary purpose: Diagnostic  Phase: N/A |
| Masking | None |
| Date of enrollment | March 25, 2024 |
| Target sample size | 100 |
| Recruitment status | Recruiting |
| Primary outcomes |  |
| Secondary outcomes |  |

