## 5.3. Roles and responsibilities

### 5.3.1. Protocol contributors

**Index of microvascular resistance (IMR)-guided management of heart transplantation**

**IMR-Heart Transplant Study**

**PROTOCOL**

**SUMMARY**

| **Study title** | INDEX OF MICROVASCULAR RESISTANCE-GUIDED MANAGEMENT OF HEART TRANSPLANTATION |
| --- | --- |
| **Short Running Title** | IMR-HEART TRANSPLANT STUDY |
| **Investigators** | [name]  [name]  [name]  [name] |
| **Study aim** | Follow-up assessment of heart transplant patients based on IMR |
| **Hypothesis** | The index of microvascular resistance will serve to reduce the number of endomyocardial biopsies in transplant patients. |
| **Study design** | Multi-center, prospective, observational |
| **Inclusion criteria** | Heart transplant patients >18 years. |
| **Exclusion criteria** | Patients presenting with hemodynamic instability after HT, including cardiogenic shock or severe coagulopathy. Patients with acute cellular rejection before intracoronary physiological assessment. Patients with bronchial asthma or bronchopathy with a positive bronchodilation test, which contraindicates the use of adenosine. Patients with epicardial coronary lesions with a resting physiological index ≤0.89 or ≤0.80 at hyperemia. Patients unlikely to cooperate in the study or with inability or unwillingness to give informed consent. |
| **Primary endpoint** | Number of biopsies performed in the first year.  IMR in transplant patients, in the first three months and one year. |
| **Secondary endpoints** | Cardiovascular mortality and IMR.  Cardiac allograft vasculopathy and IMR.  Acute cellular rejection and IMR.  IMR variation, in the first two months and at one year.  Combined endpoint of ACR, heart failure, re-transplantation, cardiovascular mortality and IMR.  Immunosuppressive therapy and IMR. |
| **Data analysis** | Observational, analytical |
| **Follow-up** | 1 year and annually for five years |

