***Statistical analysis***

The characteristics of the study population will be summarized through standard descriptive statistics. Continuous variables will be expressed as mean (± standard deviation) or median [interquartile range (IQR)], as appropriate. Discrete variables will be presented as absolute numbers and percentages. For the comparison of means, the Student's t test for independent measures or the non-parametric Mann-Whitney U test (in the case of dichotomous qualitative variables) and the ANOVA or non-parametric Kruskal test will be used as a hypothesis test. Wallis (in the case of non-dichotomous qualitative variables). For the bivariate analysis of the qualitative variables, the Chi-square test or Fisher's exact test will be used. Events will be compared between groups by using Kaplan-Meier curves. Cox regression analysis will be performed to adjust for confounding factors and to evaluate independent predictors of clinical events. A two-tailed p-value of 0.05 will be considered statistically significant. All statistical analyses will be performed by SPSS software.

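### The planned tests of association do not by themselves show whether IMR below 15 marks patients at low risk of rejection, which is what the biopsy-sparing aim needs

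*Protocol*

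**What the plan says.** The aim and the rule:

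- The Introduction and Rationale of the protocol reproduced under section 5.3.1 ends: "Our aim will be to assess if post-HT patient management may be safely modified based on IMR value".
- Its summary table gives the hypothesis: "The index of microvascular resistance will serve to reduce the number of endomyocardial biopsies in transplant patients".
- The Trial Summary (section 1) records "Primary purpose: Diagnostic".
- Under Biopsies and immunosuppressive therapy: "If the IMR is less than 15, the number of biopsies could be reduced or kept the same". Sections 3.3.1 and 3.4 say the same. At 15 or above the usual number of biopsies applies. Decisions are left to the physician, who also weighs clinical condition and other tests.

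The analysis, in section 3.12.1 and again under Statistical analysis:

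- Descriptive statistics, including counts and percentages; t or Mann-Whitney tests; ANOVA or Kruskal-Wallis; chi-square or Fisher.
- For clinical events, the stated method is: "Events will be compared between groups by using Kaplan-Meier curves".
- A Cox model is then planned, both to allow for confounders and to look for factors that predict events.
- The threshold for all tests is two-sided 0.05.
- On size and timing, section 3.12.1 says: "data will be analyzed when 100 patients have completed first year follow-up".

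Section 3.12.2 (Additional analyses) is marked not applicable. Neither statistical section mentions a confidence interval, sensitivity, predictive value or ROC measure.

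**The concern.** If a low IMR is to support fewer biopsies, two quantities matter. One is the rejection risk that remains below 15, which is one minus the negative predictive value (NPV). The other is the share of all rejections that occur below 15, which is one minus the sensitivity of IMR ≥15. A hazard ratio or a group p-value measures something else: whether risk differs between the groups. Risk can differ clearly while a good part of the rejections still falls in the low group.

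At stake is the reading of a positive result. A significant IMR–rejection association could be taken as support for reducing biopsies, although the planned analysis names no estimate, with its uncertainty, that bears on that question.

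**Working it through.** **The plan's own figure.** There is no power or precision calculation to reproduce. The 100 patients rest on centre volume: 8 × 10 = 80 to 8 × 15 = 120, midpoint 100 (if the volumes are yearly).

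**Inputs**

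- N = 100 and two-sided 0.05: section 3.12.1.
- Rejections E: the Introduction and Rationale gives up to 20% in the first year, so at most about 20. The endpoint requires grade ≥2R, and patients with rejection before the IMR measurement are excluded. Both point to fewer events, so I use 10–20.
- Share of patients below 15: not in the documents. I assume 50% and vary it from 30% to 70%.

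**Method.** For each E and split, I find the largest number of rejections x in the low-IMR group that still gives p < 0.05 in favour of low IMR. The share below 15 is x/E, sensitivity is 1 − x/E, and NPV is 1 − x/(patients below 15). Intervals are Clopper-Pearson 95%.

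**E = 20, split 50:50**

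- *Chi-square.* 6/50 v 14/50: χ² = 100 × (6×36 − 14×44)² / (50×50×20×80) = 100 × 160,000 / 4,000,000 = 4.0, p = 0.0455. With 7 v 13, χ² = 100 × (7×37 − 13×43)² / 4,000,000 = 2.25, not significant. So the share is 6/20 = 30%, sensitivity 70% (46–88%), NPV 88% (76–95%), and risk below 15 is 12% against 20% overall.
- *Fisher.* The last significant table is 5/50 v 15/50, p = 0.023. The share is 5/20 = 25%, sensitivity 75% (51–91%), NPV 90% (78–97%).
- *Log-rank boundary.* With a the share of patients below 15, HR (low v high) = exp(−1.96/√(E·a·(1−a))) = exp(−1.96/√5) = 0.42, or 2.4 for high v low. Solving a(1−e^(−H·HR)) + (1−a)(1−e^(−H)) = 0.20 for the high-group cumulative hazard H puts 31% of rejections in the low group.

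**Share of detected rejections below 15 at the weakest significant result (chi-square / Fisher)**

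| Patients below 15 | 20 events | 15 events | 10 events |
|---|---|---|---|
| 30% | 10% / 10% | 7% / 7% | 0% / 0% |
| 40% | 20% / 20% | 13% / 13% | 10% / 10% |
| 50% | 30% / 25% | 27% / 20% | 20% / 10% |
| 60% | 40% / 35% | 33% / 33% | 30% / 20% |
| 70% | 50% / 45% | 47% / 40% | 40% / 30% |

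At 20 events the log-rank boundary gives 15%, 23%, 31%, 40% and 50% down the same rows.

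**Precision.** Even an observed sensitivity of 18/20 = 90% has a 95% interval of 68–99%.

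**The case against.** Several points on the other side stand in whole or in part.

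- *The analysis fits the rejection objective as worded.* Section 2.2 lists rejection as a secondary matter and asks only about its relationship with IMR. The primary endpoint is IMR values and number of biopsies, and the protocol repeatedly calls itself observational. The diagnostic label is one registry field and does not make accuracy a formal objective. This stands, but it leaves the stated safety aim without a matching estimate.
- *The planned output is more than p-values.* Counts and percentages are planned, the low-IMR Kaplan-Meier curve shows residual risk, and the table behind the chi-square test contains the sensitivity. This stands. The remaining gap is that nothing names these figures, gives them an interval, or says that they bear on fewer biopsies.
- *A statistical analysis plan may add them.* Possible. But the protocol writes its methods out, sets the significance level and marks additional analyses not applicable, so the mismatch is in the text as it stands.
- *Reduction below 15 is optional.* Biopsies may also stay the same, at physician discretion. This stands. A reader might take the illustrated 25–31% as rejections that would be missed. The documents do not support that: rejection is defined on biopsy, so every one counted was detected.
- *Over-reading is conjecture.* No passage says that p < 0.05 for rejection would justify fewer biopsies. That is correct; the point is only that such a result would not by itself supply the evidence.
- *Accuracy measures would be biased.* Most rejections are asymptomatic and found by biopsy, according to the Introduction and Rationale. Less frequent biopsy below 15 therefore lowers detection there, which raises apparent sensitivity and NPV and inflates the high-v-low hazard ratio. This stands, and the fix must say so.

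**Conclusion.** The concern holds in a limited form. The stated analysis measures association, while the aim of safely modifying management needs the risk and the share of rejections below 15, with their uncertainty. A significant association alone would not show that IMR below 15 identifies patients at low risk.

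The size is an illustration. It is 25–31% of detected rejections below 15 with 100 patients, 20 events and a 50:50 split. It is 10–50% at 20 events across splits of 30–70%, and 0–47% at 10–15 events by chi-square or Fisher. The split is my assumption and 20 events is the protocol's upper bound, so a fixed figure of 30% cannot be read from the documents. With few events and few patients below 15, even the weakest significant result can leave little or nothing in the low group.

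**What to change.** Add to section 3.12.1 and to the matching Statistical analysis text:

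1. For early IMR at the protocol's cut-off of 15, report the one-year risk of rejection (≥2R) at IMR <15 (1 − NPV), the sensitivity of IMR ≥15, and the share of all rejections at IMR <15, each with a 95% confidence interval. The last two are complements, so one interval determines the other.
2. State that these estimates, rather than the hazard ratio or its p-value, bear on whether IMR could support fewer biopsies.
3. Report the number of biopsies by IMR group. State that less frequent biopsy below 15 biases sensitivity and NPV upward and inflates the hazard ratio.
4. Repeat the analysis in patients whose biopsy schedule was not reduced, as a sensitivity analysis. Note that physician discretion selects this subset, so it does not remove the bias.

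The cost is a short addition to the analysis text, using biopsy and event data that the study's endpoints already require. The downside is wide intervals at 20 or fewer events and a more modest conclusion.
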